## Abstract

**Introduction:**

OSAS is a common yet underdiagnosed condition, particularly among patients with head and neck cancers (HNC). Anatomical changes caused by the tumor or its treatments—surgery, radiotherapy, or chemotherapy—can promote the onset of OSAS. However, fatigue in these patients is often attributed solely to the cancer treatment itself, which may delay appropriate diagnosis and management.

**Methods:**

This prospective single-center study aims to assess the clinical feasibility of OSAS screening in patients with HNC using an innovative mobile application, *Apneal*, which uses smartphone sensors to detect nocturnal respiratory events through an artificial intelligence algorithm. Fifty adult patients diagnosed with HNC will be included. Each patient will perform two home-based overnight recordings using the *Apneal* application: one at the time of diagnosis and another six months after local treatment. Clinical and quality-of-life questionnaires will be completed. The estimated AHI will be compared with symptomatology and, if necessary, confirmed by a standard respiratory polygraphy.

**Expected Results:**

The primary outcome is the proportion of patients for whom *Apneal* data are usable at the 6-month follow-up after treatment. Secondary objectives include assessing the incidence of OSAS according to the oncologic treatments received, identifying high-risk profiles, and evaluating the impact of OSAS on quality of life.

**Discussion:**

This study could pave the way for a systematic, simple, low-cost, and non-invasive OSAS screening in patients with HNC. Ultimately, the goal is to enable a more personalized and comprehensive approach to care in this vulnerable population.

## Introduction

Obstructive Sleep Apnea Syndrome (OSAS) is a common condition in France, affecting approximately 4–10% of the population, but it remains underdiagnosed [1]. This syndrome is defined by episodes of obstructive apnea and/or hypopnea accompanied by daytime sleepiness. It can lead to fatigue, cardiovascular complications, motor vehicle accidents, and depressive or anxiety disorders [1]. The pathophysiology of OSAS is primarily based on a narrowing of the pharyngolaryngeal airway during sleep and/or a loss of function in the pharyngeal dilator muscles [2].

Head and neck cancers (HNC) account for approximately 15,000 new cases per year in France in 2018 according INCa (Institut National du Cancer) [3]. These cancers and their treatments (radiotherapy, chemotherapy, surgery with or without reconstruction) cause significant anatomical changes in the upper airway. Given that the main characteristic of OSAS is upper airway collapse, additional factors may further exacerbate this obstruction in this group of patients. These include anatomical abnormalities (such as hypertrophied soft tissues or narrowing of the pharyngeal space due to a mass effect) and neurological factors (such as neurosensory dysfunction affecting the feedback loop between the upper airways and the pharyngeal dilator muscles).

Therefore, it is reasonable to assume that patients with HNC may be at increased risk of developing OSAS. An increasing number of studies support this association, although the specific risk factors have not yet been clearly identified [4]. However, this condition appears to be underdiagnosed in this group of patients, as the chronic fatigue experienced by this population seems to be attributed to the cancer itself and its various treatments. Moreover, the distinction between sleepiness, the predominant symptom of obstructive sleep apnea (OSA), and asthenia is not always clearly made by either practitioners or patients.

Given these findings, it seems relevant to explore the implementation of OSAS screening in patients newly diagnosed with HNC and during follow-up. The aim of this work is to enable earlier intervention and improve the overall quality of life of these patients during their cancer care. Currently, fatigue in patients treated for HNC is often attributed to cancer treatments, and the contribution of a coexisting condition such as OSAS is rarely considered.

Access to polysomnography or ventilatory polygraphy remains difficult and costly for healthcare systems. For HNC patients, whose follow-up is already complex, a rapid diagnosis of OSAS would be particularly beneficial. Recently, new diagnostic tools have been developed for easy home use, based on tracheal sounds [5], mandibular movements [6], or motion-sensing mattresses [7]. However, these devices require dedicated equipment.

Our project aims to simplify the diagnosis of OSAS and reduce its cost. In this context, we have partnered with a start-up that has developed a smartphone-based medical application called APNEAL [8].

APNEAL is currently undergoing validation in a European clinical trial. It has already been tested in a preliminary French clinical study (Hôpital Bichat, AP-HP) to confirm its feasibility [8]. The application uses smartphone sensors, worn on the chest overnight, to detect apneas and hypopneas using an AI-based algorithm. In the first study, APNEAL’s results were compared to simultaneous polysomnography recordings and showed promising accuracy. In this first study conducted at Bichat Hospital in patients with a high probability of having obstructive sleep apnea syndrome (OSAS), it was shown that respiratory events could be accurately detected using smartphone sensors such as the microphone, gyroscope, and accelerometer. The results were compared with non-expert scorers analyzing polysomnography recordings and showed a sensitivity of 0.91 and a positive predictive value (PPV) of 0.89 for an apnea–hypopnea index (AHI) threshold of 15 [8].

The app is not yet commercially available.

Our study aims to assess the clinical feasibility of using this application in patients with HNC. The goal is to enable early detection of OSAS and, through repeated recordings, to identify patients who may be at higher risk of developing this condition.

## Materials and methods

This clinical study will be a prospective, monocentric, non-randomized trial conducted in a French department of Otorhinolaryngology and Head and Neck Surgery, expert in sleep disorder.

Inclusion criteria are as follows: adult patients affiliated with the national health insurance system, presenting with a suspected HNC, currently undergoing diagnostic work-up, and having signed an informed consent form. Eligible malignant tumor sites include the nasal cavities, sinuses, oral cavity, nasopharynx, oropharynx, hypopharynx, larynx, suspicious cervical lymphadenopathy and the parotid gland.Exclusion criteria include patients with a history of OSAS, prior treatment for HNC, minors, individuals under legal protection (guardianship or conservatorship), and later, patients whose lesion is not confirmed as malignant.

### Study population

Once included, each patient will follow an organized diagnostic pathway for suspected HNC. The study aims to enroll 2–3 patients per week over 6 months, totaling approximately 50 participants. If inclusion criteria are met, study participation will be proposed at the first consultation. Each patient will receive an information leaflet and provide written informed consent. Study logistics, potential risks, and procedures will be explained (V0).

### Study design

A second visit (V1) will include a standardized sleep consultation in accordance with the Association Française du Sommeil en ORL (AFSORL) [9], including the **Epworth Sleepiness Scale** [10] and **BOSS (Bordeaux Sleepiness Scale)** [11] for drivers. Demographic and clinical data will be collected (age, sex, comorbidities, treatments), along with several self-administered questionnaires:

Snoring and sleep quality questionnaire (AFSORL) [9],EORTC QLQ-C30 (European Organisation for Research and Treatment of Cancer Quality Of Life) [12],EORTC H&N35 (European Organisation for Research and Treatment of Cancer Head and Neck) [13].

A loan smartphone (Samsung Galaxy XCover 7) with the APNEAL application pre-installed will be provided. Patients will conduct a home-based overnight recording under their usual sleeping conditions.

At a subsequent hospital visit (V2), the smartphone will be returned. Patients will complete a feedback questionnaire (Fig 1) on their experience with the application, and some will participate in semi-structured interviews.

**Fig 1 pone.0346607.g001:**
[figure not shown]
Post-use questionnaire for the APNEAL Application.

Usable data will be extracted via a certified medical drive provided by MITRAL (developer of APNEAL), including recording duration and the estimated Apnea–Hypopnea Index (AHI).

Subsequent clinical management will be based on the AHI, symptomatology, and individual risk factors, following the flowchart (Fig 2). Given that the application is not yet officially validated at the start of the study, we have agreed that any AHI between 15 and 30 with severe cardiovascular comorbidity will require confirmation via a standard ventilatory polygraphy (*Cidelec*).

**Fig 2 pone.0346607.g002:**
[figure not shown]
Flowchart for the management of the patient included according to symptomatology and the result given by the Apneal application.

At the 6-month post-treatment follow-up visit (V3), in addition to the standard oncological follow-up consultation, patients will undergo a second sleep consultation integrated into their routine visit. This will include: a sleep consultation, the BOSS (Bordeaux Sleepiness Scale) questionnaire if the patient is a driver, and repeated completion of the self-administered questionnaires (Snoring and Sleep Quality Questionnaire per AFSORL, EORTC QLQ-C30, and H&N35). A second overnight home recording using the APNEAL application on the loan smartphone will also be performed. The V3 visit will take place 6 months after completion of the patient’s treatment (which is estimated to last approximately 3 months), except for metastatic patients receiving systemic therapy, who will be seen approximately 9 months after initiation of treatment.

During a subsequent visit (V4), the patient will return the smartphone and complete questionnaires regarding their user experience. Clinical management will again follow the predefined flowchart (Fig 3).

**Fig 3 pone.0346607.g003:**
[figure not shown]
Participant timeline.

The study has not yet started. Patient enrollment is scheduled to begin in October 2025, recruitment will be completed by May 2026, and patient follow-up is expected to finish around February 2027. The results are anticipated by May 2027.

### APNEAL: Instructions for use

The smartphone will be attached to the patient’s chest using adhesive tape, with the screen facing outward (Fig 3). To avoid burns from overheating and potential skin injuries from the adhesive, it is recommended to secure the phone over a comfortable piece of nightwear. The smartphone must be set to “airplane mode” to prevent the emission of electromagnetic waves. We will place the smartphone ourselves to ensure it is correctly positioned for the study. Using artificial intelligence algorithms, APNEAL analyzes the patient’s position during the night, the probability of breathing, and the probability of snoring in order to generate interpretable signals Fig 4.

**Fig 4 pone.0346607.g004:**
[figure not shown]
Photo showing how the smartphone should be attached [14].

### Judgement criteria

The primary endpoint of the study is to evaluate the feasibility of screening for obstructive sleep apnea syndrome (OSAS) in clinical practice among patients with head and neck cancers, using the APNEAL application.

The secondary endpoints are to examine the incidence of OSAS in patients treated for HNC depending on the therapeutic strategy used, in order to identify patient profiles at higher risk of developing OSAS, and to assess the impact on their quality of life.

To achieve this, the primary evaluation criterion is the proportion of patients with usable data collected 6 months after the end of local oncological treatment, with an interim analysis following the first consultation and the first overnight recording.

The secondary evaluation criteria include measuring the evolution of the apnea-hypopnea index (AHI) during cancer management to identify risk factors, and assessing the changes in quality of life indicators throughout the treatment process.

### Statistical analysis

The planned number of patients is 30. However, considering the risk of some patients not completing the study, it is entirely feasible to recruit up to 50 patients. For a 60% success rate of patients with usable collected data (i.e., 30 out of 50 patients), the 95% confidence interval is between 45.2% and 73.6%.

For the primary evaluation criterion, the proportion of patients with usable collected data will be calculated along with its exact 95% confidence interval. Regarding the incidence of OSAS, the first secondary objective, analysis will focus on OSAS classification (mild, moderate to severe) according to the therapeutic strategy applied. To identify patients at higher risk of developing OSAS (second secondary objective), we will measure the AHI (Apnea-Hypopnea Index) throughout the care process. Changes in AHI scores, whether treated as quantitative or categorical data ([5–15]: mild OSAS; [15–30]: moderate OSAS; ≥ 30: severe OSAS), will be analyzed in relation to patients’ clinical characteristics and scale scores.

Statistical analyses will rely on standard univariate tests depending on the type of variables considered: Chi-square test, Fisher’s exact test, ANOVA, Pearson or Spearman correlation. Multivariate analyses will be considered depending on the analytical approach and the preliminary results (ANOVA, linear regression, logistic regression). A factor analysis using principal component analysis (PCA) may be performed to identify patient profiles, adhering to the validity conditions: the number of variables (quantitative or categorical with ≥3 categories) must correspond to at least 10× to 5 × the number of patients (i.e., 5–10 variables in the multifactorial model).

For the third secondary objective, which is to assess the impact on quality of life, changes in quality of life scores before and after treatment will be analyzed using a paired-sample test (Student’s paired t-test for V2 and V4, or the Wilcoxon signed-rank test).

All statistical analyses will be performed with a two-sided alpha risk of 5%, using IBM SPSS Statistics for Windows, Version 23.0. Armonk, NY: IBM Corp.

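### The planned number is given as 30 in one place and about 50 in others, and the stated precision holds only if 50 patients are analysed, a number and denominator the plan does not secure

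*Protocol article*

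**What the plan says.** **Sample size.** The Statistical analysis section opens with "The planned number of patients is 30" and continues: "considering the risk of some patients not completing the study, it is entirely feasible to recruit up to 50 patients". The Abstract (Methods) says "Fifty adult patients diagnosed with HNC will be included", and the Study population section aims for approximately 50 participants.

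**Precision.** The worked example reads "For a 60% success rate of patients with usable collected data (i.e., 30 out of 50 patients", for which "the 95% confidence interval is between 45.2% and 73.6" percent. An exact 95% interval is planned for the primary proportion.

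**Who enters and who leaves.** Materials and methods admits patients with suspected head and neck cancer (HNC) who are still being worked up. Its exclusion list ends with "later, patients whose lesion is not confirmed as malignant".

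**Primary criterion.** Judgement criteria defines it as the "proportion of patients with usable data collected 6 months after the end of local oncological treatment". The denominator is not named there or in the Statistical analysis section. The V3 paragraph of the Study design section sets that visit 6 months after treatment ends, "except for metastatic patients receiving systemic therapy, who will be seen approximately 9 months after initiation of treatment".

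**The concern.** The trial has one primary result, a single proportion with its interval, so its credibility depends on knowing which patients are in the denominator and how many there will be. Four statements leave this unsettled.

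- The planned number is 30 in one section and about 50 in two others.
- The precision is quoted for 50, yet enrolment comes before confirmation of malignancy and unconfirmed patients are then removed.
- The only reason given for 50 rather than 30 is non-completion. The same two numbers then form the 60% rate of usable data. A reader cannot tell how much of the missing 40% is patients lost before V3 and how much is recordings that failed.
- The primary criterion is timed from the end of local treatment. Metastatic patients on systemic therapy may have had none, yet they are given a V3.

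At stake are the precision the study can claim and the meaning of its main figure. A low proportion could reflect deaths and withdrawals in a sick population, or an application that does not record well in these patients. Those two findings call for different next steps.

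**Working it through.** **Inputs from the Protocol article.** Planned number 30; recruitment up to 50; example of 30 usable out of 50; stated interval 45.2% to 73.6%; exact method; two-sided 5% (all Statistical analysis). Enrolment of fifty (Abstract) or about 50 (Study population). Later removal of unconfirmed lesions (Materials and methods). The documents give no rate of benign findings, no completion rate and no rate of unusable recordings, so values for these are assumptions, marked as such.

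**Formula.** For x usable out of n, the exact (Clopper-Pearson) 95% limits are the 0.025 quantile of Beta(x, n − x + 1) and the 0.975 quantile of Beta(x + 1, n − x).

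**Step 1: reproduce the plan's figure.** With x = 30 and n = 50, the limits are 45.18% and 73.59%. This matches the plan. Wald (46.4% to 73.6%) and Wilson (46.2% to 72.4%) do not, so the plan used the exact method with n = 50.

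**Step 2: hold 60% and change only the number analysed.**

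| Analysed | Basis | Usable | Exact 95% CI | Width (points) |
|---|---|---|---|---|
| 50 | plan's example | 30 | 45.2% to 73.6% | 28.4 |
| 45 | 10% of 50 benign (assumed) | 27 | 44.3% to 74.3% | 30.0 |
| 40 | 20% of 50 benign (assumed) | 24 | 43.3% to 75.1% | 31.8 |
| 30 | plan's planned number | 18 | 40.6% to 77.3% | 36.7 |

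**Step 3: what the 60% can mean.** Going from 50 to 30 implies a loss of (50 − 30)/50 = 40%, a rate the plan does not state. The usable share of all patients is the share completing multiplied by the share usable among completers. Different pairs give the same 30/50:

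- 30 completers, all usable: 30/50 × 30/30 = 60%.
- 40 completers, 75% usable: 40/50 × 30/40 = 60%.
- 50 completers, 60% usable: 50/50 × 30/50 = 60%.

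Usability among completers could therefore lie anywhere from 60% to 100% with the same primary result and the same interval.

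**Step 4: compare the timing statements.** Judgement criteria counts 6 months from the end of local treatment. Study design counts 6 months from completion of treatment, estimated at about 3 months, and for metastatic patients on systemic therapy about 9 months from its start. As 3 + 6 = 9, the two visit rules are consistent with each other. The word local is what does not fit: read literally, it gives no reference date to a patient who has no local treatment, and so leaves open whether that patient counts.

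**The case against.** **The worked denominator is 50, and the interval is right.** This stands. No section computes a proportion out of 30. The conflict lies in the planned number and in who will be analysed, not in the arithmetic.

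**Fifty could mean fifty confirmed cases.** The Abstract calls them patients diagnosed with HNC. If enough were enrolled to leave 50 confirmed, the quoted interval would apply. But Study population sets about 50 as the number enrolled, with participation proposed at the first consultation and the diagnostic pathway following inclusion. The plan mentions no replacement or allowance for benign findings.

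**Counting non-completion as failure is legitimate.** This also stands. The aim is feasibility of screening in clinical practice, and a patient with no recording was not screened. The composite is a sound primary measure; what it lacks is a companion figure.

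**Detail may sit in the full protocol.** Full analysis-set definitions and data-handling rules are fairly left there. The two sample sizes and the two timing statements, however, are in this text and do not agree.

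**Stronger readings to avoid.** A reader might infer that the plan treats 30 as expected completers and assumes every one yields a usable recording. The text calls the 30 patients with usable data, and Step 3 shows that other splits give the same figure. A reader might also infer that the choice of denominator could reverse the study's conclusion, or that the plan fails because its lower limit is below 50%. The plan states no hypothesis and no threshold, so there is no pass mark to cross.

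**Conclusion.** The concern holds in a limited form and should be fixed. The interval of 45.2% to 73.6% is correct for 30/50 but applies only if 50 patients are analysed, which does not follow from enrolling about 50 suspected cases. At 60% usable, the width grows from 28.4 points to 31.8 with 40 analysed and 36.7 with 30. The loss of precision is therefore modest unless 30 really is the intended number. The figure of 40 rests on an assumed 20% benign rate; 30 is the plan's own number.

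The more important gap is one of meaning. The 60% combines attrition and unusable recordings in unknown shares, and the wording of the primary criterion leaves metastatic patients on systemic therapy neither clearly in nor clearly out.

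**What to change.** 1. Replace the 30 and the 50 with one enrolment target and one expected number analysed. State the assumed share of lesions not confirmed as malignant that links them, and restate the exact interval for the number analysed.
2. Define the primary proportion over all included patients with confirmed HNC. Count those with no V3 recording, through death, withdrawal or the recording not being done, as not usable. Reconcile the timing in Judgement criteria with the V3 that Study design gives metastatic patients on systemic therapy, so that it is clear how they enter the proportion.
3. Report alongside it, with an exact 95% interval, the proportion usable among patients who attempted the V3 recording. This is the measure of technical feasibility; the primary proportion, which deliberately includes attrition, remains the measure of feasibility in practice.

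The cost is a few sentences of wording, one extra proportion and a slightly wider stated interval. No additional visits or data are needed beyond noting whether each V3 recording was attempted. The changes should be made before the data are seen.

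### Incidence of OSAS by treatment strategy is analysed as OSAS class by strategy, not restricted to patients negative at the first recording, so it yields prevalence

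*Protocol article*

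**What the plan says.** All references are to the protocol article.

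- **Objective (Judgement criteria).** One secondary endpoint is to "examine the incidence of OSAS in patients treated for HNC depending on the therapeutic strategy used", with the aim of finding patient profiles at higher risk of developing OSAS.
- **Analysis (Statistical analysis).** For this objective, "analysis will focus on OSAS classification (mild, moderate to severe) according to the therapeutic strategy applied". No time point, denominator or baseline condition is attached.
- **Next objective (same section).** The search for higher-risk patients is handled separately: "Changes in AHI scores, whether treated as quantitative or categorical data" are to be related to clinical characteristics and scale scores. The OSAS classes start at an AHI of 5 (5–15 mild, 15–30 moderate, 30 or more severe).
- **Entry (Materials and methods).** The exclusions include "patients with a history of OSAS, prior treatment for HNC". A positive first recording is not among them.
- **Recordings (Abstract, Methods).** There are two per patient: "one at the time of diagnosis and another six months after local treatment".
- **Background (Introduction).** OSAS is described as "affecting approximately 4–10% of the population, but it remains underdiagnosed", and the same section says it appears to be underdiagnosed in head and neck cancer patients too.
- **After the first recording (Study design).** "Subsequent clinical management will be based on the AHI, symptomatology, and individual risk factors", following a flowchart that is not reproduced in the text available.

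**The concern.** Incidence counts new cases among people who did not have the condition at the start. A table of OSAS class by treatment strategy describes a state, which is prevalence, whichever recording supplies the class. The protocol's own reasoning makes the difference matter. It excludes only OSAS that is already known, says the condition is often missed in this population, and describes airway narrowing by tumour mass, which is present before treatment.

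Two things are at stake. First, the figure reported as incidence would be too high to the extent that baseline cases persist. Second, the comparison between strategies is exposed. The study is non-randomized, and the Discussion links tumour site to OSAS. If site also influences the choice of treatment, baseline OSAS will differ between strategies, and that difference would carry into a class-by-strategy table as if it were new onset. The Discussion justifies a prospective design by noting that most published work gives post-treatment prevalence from retrospective data. An unrestricted class table at follow-up would share that limitation even though a baseline recording is taken.

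**Working it through.** **1. The plan's own figure.** The only computed figure is the interval for 30 of 50 patients with usable data. The exact (Clopper-Pearson) 95% interval for 30/50 is 45.18% to 73.59%, which reproduces the stated 45.2% to 73.6%. It concerns the primary criterion. No stated figure rests on the point made here.

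**2. Inputs for the illustration.** The documents give neither the proportion positive at the first recording nor the new-onset rate in this population, so both are assumptions:

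- b = proportion positive at the first recording, ranged from 4% to 50%. The 4% and 10% values are the article's general-population range; the higher values are assumed.
- i = new onset among baseline negatives, set at 10% and 20% (15% in step 4).
- No remission: everyone positive at baseline stays positive at V3.

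**3. What a V3 class table would show.** The proportion positive at V3 is P = b + (1 − b)·i. The share of those positives who were already positive is b/P. For example, with b = 10% and i = 20%, P = 0.10 + 0.90 × 0.20 = 0.28, and 0.10/0.28 = 36%.

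| b | P (i = 10%) | already positive | P (i = 20%) | already positive | at risk of 30 | at risk of 50 |
|---|---|---|---|---|---|---|
| 4% | 13.6% | 29% | 23.2% | 17% | 28.8 | 48 |
| 10% | 19.0% | 53% | 28.0% | 36% | 27 | 45 |
| 20% | 28.0% | 71% | 36.0% | 56% | 24 | 40 |
| 30% | 37.0% | 81% | 44.0% | 68% | 21 | 35 |
| 40% | 46.0% | 87% | 52.0% | 77% | 18 | 30 |
| 50% | 55.0% | 91% | 60.0% | 83% | 15 | 25 |

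The at-risk columns are N(1 − b). Across this range, 17% to 91% of V3 positives would be pre-existing cases.

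**4. Comparison of strategies with identical new onset.** Take i = 15% in both.

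- Strategy A, b = 20%: 0.20 + 0.80 × 0.15 = 32%.
- Strategy B, b = 40%: 0.40 + 0.60 × 0.15 = 49%.

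The apparent difference is (0.40 − 0.20) × (1 − 0.15) = 17 percentage points, when the true difference in new onset is zero. With 10% and 40% at baseline the figures are 23.5% and 49%.

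**5. Dependence on the no-remission assumption.** If a fraction r of baseline positives is negative at V3, then P = b(1 − r) + (1 − b)·i, and the apparent difference becomes (b_B − b_A)(1 − r − i). It shrinks as r grows, vanishes when r + i = 1 and reverses beyond that. The 17 points are therefore the no-remission case, not a forecast.

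**The case against.** The strongest defence is that the text is silent rather than wrong. It does not say that V3 class alone will be used, or that patients positive at the first recording will be counted as new cases. Denominators for a secondary analysis are often left to a full protocol or analysis plan, and this is a condensed article. The baseline recording exists, the evolution of AHI is a named secondary criterion, and changes in AHI, including by category, are analysed. The data needed to separate new from existing OSAS are collected and partly used.

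Much of this is fair, and it limits the point. But the article does more than omit a detail: it names the analysis for incidence, and that analysis as worded does not measure incidence. The authors specified change for the second objective and did not do so for the first.

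Four stronger readings are tempting, and the documents do not support them:

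- **That pre-existing OSAS is attributed to treatment.** The plan makes no causal statement. The tests are associations in a non-randomized study.
- **That the search for higher-risk patients fails for the same reason.** That objective uses change in AHI from baseline. Its exposure is narrower: management begun after the first recording may affect the second AHI. Who is managed, and how, depends on a figure that is not shown, so this calls for a sensitivity analysis only.
- **That a particular inflation is to be expected.** The rates above are assumed. At a baseline of 10% with 20% new onset the table shows 28%; the large multiples need high assumed baseline rates and no remission.
- **That AHI 15 should be the main cut-off because accuracy is quoted there.** The protocol classifies OSAS from AHI 5. A cut-off of 15 would place patients with mild baseline OSAS in the at-risk set, count their progression as new disease, and miss new mild OSAS.

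**Conclusion.** The point holds for the first secondary objective. OSAS class by strategy, without restriction to patients negative at the first recording, estimates prevalence and not incidence. Baseline differences between non-randomized strategies can then pass for differences in new onset. The illustrative size is 32% against 49% at V3 with equal 15% new onset, assuming 20% and 40% baseline positivity and no remission; the actual size cannot be known from the documents. The primary feasibility criterion and its interval are untouched. This should be corrected before analysis, but it is not a flaw that threatens the trial.

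**What to change.** In the Statistical analysis section, or in the analysis plan:

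1. Define incident OSAS as AHI at or above 5, the protocol's own lower limit for OSAS, at V3 among patients below 5 at the first recording who have both recordings usable. Report it by strategy with exact 95% confidence intervals.
2. Optionally add, as a supporting analysis, new AHI of 15 or more among patients below 15 at the first recording.
3. Report prevalence at the first recording, prevalence at V3 and class transitions by strategy, each labelled as such.
4. Record whether OSAS management was started between the two recordings, and show the AHI-change analysis with and without those patients.

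No additional recording is needed. The cost is analysis wording, one recorded item if it is not already collected, and precision. If 30 patients have both recordings usable, baseline positivity of 10%, 30% or 50% leaves 27, 21 or 15 at risk. For the same observed proportion, interval width grows roughly as the square root of the ratio of sample sizes: √(30/27) = 1.05, √(30/21) = 1.20 and √(30/15) = 1.41, before any split by strategy. Estimates by strategy will be imprecise and should be presented as descriptive.

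### The abstract's objective is the effect of OSAS on quality of life, but the only test assigned to it is a before/after comparison without AHI or OSAS

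*Protocol article*

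**What the plan says.** The protocol article words the quality-of-life objective in three places, not all the same way.

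- **Abstract, Expected Results:** the objective is "evaluating the impact of OSAS on quality of life". OSAS is the exposure and quality of life the outcome.
- **Judgement criteria:** after OSAS incidence and OSAS risk profiles, the aim is "to assess the impact on their quality of life", without repeating what the impact is of. The matching evaluation criterion is "assessing the changes in quality of life indicators throughout the treatment process".
- **Statistical analysis:** for the third secondary objective, "changes in quality of life scores before and after treatment will be analyzed using a paired-sample test", specified as "Student’s paired t-test for V2 and V4, or the Wilcoxon signed-rank test".

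One other sentence in Statistical analysis could link AHI to questionnaire scores. Under the second secondary objective (who is at higher risk), changes in AHI "will be analyzed in relation to patients’ clinical characteristics and scale scores". The scales are not named.

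**The concern.** An analysis of the impact of OSAS has to compare patients, or visits, that differ in OSAS. The paired test does not: it asks whether the cohort's mean score differs before and after cancer care. Its result combines the tumour, surgery, radiotherapy, chemotherapy and whatever OSAS adds.

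The Introduction and Discussion argue that fatigue in these patients is put down to cancer treatment while OSAS is overlooked. Separating those two sources is the reason for asking the question, and the named test cannot separate them. A significant change would not be evidence of an OSAS effect, and a null result would not be evidence against one.

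This is not detail that a condensed article leaves to a fuller document. The article does name the analysis for this objective, and that analysis answers a different question.

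**Working it through.** **1. The plan's own figure.** The only statistical result in the article is the interval for 30 of 50 patients with usable recordings. The exact (Clopper-Pearson) limits are the 2.5% quantile of Beta(30, 21) = 45.18% and the 97.5% quantile of Beta(31, 20) = 73.59%. These match the stated 45.2% to 73.6%. That figure concerns the primary endpoint; none is given for quality of life.

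**2. Objective against analysis.**

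| Element | Abstract objective | Test in Statistical analysis |
|---|---|---|
| Outcome | quality of life | quality of life |
| Exposure | OSAS | none; time (before/after treatment) |
| AHI or OSAS term | needed | absent |
| Adjustment for treatment | needed to separate the two | absent |

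**3. What the paired test responds to.** Inputs from the article: two-sided 5% level, 30 patients planned, up to 50 recruited. The article gives no SD, effect size or AHI correlation for quality of life, so these are assumptions: standardised mean change in quality of life m = 0 or -0.5, and correlation r between AHI change and quality-of-life change of 0 or -0.5.

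Model, 4,000 simulated trials per row: quality-of-life change = m + r·A + √(1 − r²)·e, where A (standardised AHI change) and e are independent standard normal. Share of trials significant:

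| n | m | r | Paired t-test | Correlation with AHI change |
|---|---|---|---|---|
| 30 | -0.5 | 0 | 77% | 5% |
| 30 | -0.5 | -0.5 | 75% | 82% |
| 30 | 0 | -0.5 | 5% | 84% |
| 30 | 0 | 0 | 5% | 5% |
| 50 | -0.5 | 0 | 94% | 5% |
| 50 | -0.5 | -0.5 | 93% | 97% |
| 50 | 0 | -0.5 | 6% | 97% |
| 50 | 0 | 0 | 5% | 5% |

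At a given m, the paired test gives the same answer, within simulation error, whether or not AHI matters. It follows m only. Part of m could in truth be due to OSAS, but the test cannot say how much.

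**4. What an analysis using AHI could detect.** Fisher z approximation: the correlation needed for 80% power is tanh[(1.960 + 0.842)/√(n − 3)].

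- n = 30: tanh(2.802/5.196) = tanh(0.539) = 0.49.
- n = 50: tanh(2.802/6.856) = tanh(0.409) = 0.39.

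Power = Φ(atanh(r)·√(n − 3) − 1.960):

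| Size of r | n = 30 | n = 50 |
|---|---|---|
| 0.3 | 36% | 56% |
| 0.4 | 60% | 83% |
| 0.5 | 81% | 96% |

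These are unadjusted; adding covariates lowers power somewhat.

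**The case against.** **The paired test matches the stated criterion.** The Judgement criteria section measures change in quality of life over treatment, and a paired test does exactly that. Only the abstract names OSAS outright as the cause. This stands in part: the defect can be read as inconsistent wording, and rewording the abstract would remove the contradiction. It would also give up the question that the Introduction motivates. In Judgement criteria, the phrase directly follows OSAS incidence and risk, so OSAS is its natural subject.

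**The plan may relate AHI to quality of life elsewhere.** A reader might infer that the whole plan never does so. The article does not support that. The unnamed scale scores under the second objective could include the EORTC questionnaires, and a correlation has no direction, so that analysis might yield an unadjusted AHI association. But the sentence serves the risk-profile objective, treats AHI change as the outcome and does not name quality of life; the scales could equally be Epworth or BOSS. It does not give the third objective an analysis.

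**Dropout.** A reader might also infer that only 30 of 50 patients will have paired quality-of-life data, and that the paired test is therefore biased by a known amount. The 30 of 50 is an illustrative rate of usable APNEAL recordings, and a questionnaire can be complete when a recording is not. The article expects some non-completion but gives no questionnaire rate. Even the direction of any bias depends on an assumed dropout mechanism.

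**Conclusion.** The concern holds for the analysis assigned to the third secondary objective. Followed as written, it gives no estimate of the effect of OSAS on quality of life, which is the objective stated in the abstract. That rests on the text alone. The simulation only illustrates it, and its percentages depend on the assumed mean change and correlation.

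It would be too strong to call this a defect of the trial as a whole. The primary outcome is usable data at six months, and neither that result nor the data collection is affected. It would also be too strong to say that adding AHI delivers the impact of OSAS: with 30 to 50 observational patients, an AHI coefficient is an adjusted association, and a moderate one could easily be missed. This is a should-fix.

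**What to change.** - **Add an analysis for the third secondary objective.** Regress the V3 EORTC score (or its change from V1) on AHI at V3 (or AHI change), adjusted for the V1 score and treatment strategy. Report the AHI coefficient with its 95% CI as an exploratory adjusted association.
- **Keep the paired test** as a description of change over treatment.
- **Align the wording** of the objective in the abstract, Judgement criteria and Statistical analysis. If only change over treatment is meant, the abstract should say so.
- **Reconcile the visits.** The paired test names V2 and V4, but Study design schedules the EORTC questionnaires at V1 and V3 and lists only user-experience questionnaires at V2 and V4.

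The cost is wording and a modest amount of analysis, because AHI, treatment and EORTC scores are already collected. The downside is that the regression uses only patients with both usable recordings and completed questionnaires, so it shares the completer restriction of the paired test, may use fewer patients, and will be imprecise.
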